### Interventions

TUS will be administered using the NeuroFUS system (Sonic Concepts), which consists of a 4-element annular array transducer (CTX-500; Sonic Concepts) with a diameter of 60 mm and a fundamental frequency of 500 kHz. The transducer is powered by a programmable radiofrequency amplifier (TPO-203; Sonic Concepts), which controls the phasing of the 4 elements to adjust the sonication depth. A neuronavigation system (Brainsight; Rogue Research Inc) will be used to identify the stimulation site and precisely monitor and maintain the position and orientation of the transducer throughout all treatment sessions.

The stimulation target will be either M1, corresponding to the most painful region, or the PSI, both located contralateral to the pain. When the M1 hand area is selected, the motor hot spot identified through cortical excitability measurements using transcranial magnetic stimulation (TMS) will be used. The PSI will be localized on individual 3D magnetic resonance imaging (MRI) in the navigation system according to the previously reported “quadrant-within-a-quadrant” method [29]. For all other targets, stimulation sites will be determined on the individual MRI with reference to the Montreal Neurological Institute-Hospital (MNI) space standard atlas integrated into the navigation system [30]. The M1 foot target will be defined using the MNI coordinate (–7 or +7 mm; –27 mm and 59 mm) as the default location and subsequently adjusted based on each participant’s structural MRI. The central sulcus will be identified on axial images and traced medially, whereas the marginal ramus of the cingulate sulcus will be identified on the midsagittal image. The target will be placed in the anterior part of the paracentral lobule, immediately anterior to the central sulcus. If the default MNI coordinate falls within a sulcus, the target will be adjusted to the nearest cortex within the M1 foot area. Because the TUS device achieves optimal efficiency at a focal depth of 48.5 mm, an ultrasound gel pad of appropriate thickness (Echo Gel Pad; Yasojima Proceed Co., Ltd) will be placed between the transducer and the scalp to adjust the distance from the transducer surface to the stimulation target to within 43 to 54 mm. Stimulation parameters will be as follows: pulse duration of 10 ms, pulse repetition interval of 100 ms (10 Hz), pulse train duration of 10 seconds, pulse train repetition interval of 30 seconds, duty cycle of 10%, 20 trains, total stimulation duration of 580 seconds, and spatial peak pulse average intensity in free water of 30 W/cm^2^. The temporal stimulation pattern will be designed with reference to stimulation paradigms used in rTMS for refractory NP, consisting of intermittent 10-Hz pulse trains delivered over approximately 10 minutes [17,18,31]. Selected acoustic parameters, including stimulation frequency and intensity, will be informed in part by the human TUS protocol reported by Osada et al [32] using the same TUS device, although the temporal stimulation parameters will be modified for the present study. The stimulation intensity will be set within a range that has previously been applied without serious adverse events and remained within the safety limits recommended by the recent International Consortium for Transcranial Ultrasonic Stimulation Safety and Standards consensus statement [33]. The mechanical index, estimated using the TUS calculator [34] at a focus depth of 43 mm, was 1.32. On the basis of simulations reported by Osada et al [32], the maximum temperature increase will be estimated to be 0.5 °C in brain tissue and 0.8 °C in the skull. Extrapolating these values according to the effective sonication time used in the present study will yield conservative maximum estimates of 0.83 °C for brain tissue and 1.33 °C for the skull assuming no heat dissipation [32]. As the increase remained below 2 °C and the intervention time was less than 10 minutes, the thermal dose was estimated to be below 0.25 CEM43. The thermal index for the skull was calculated as 1.9. These values are within the safety thresholds recommended by the recent International Consortium for Transcranial Ultrasonic Stimulation Safety and Standards consensus on TUS safety [33].

Treatment will be administered with the participant seated comfortably in a reclining chair. Ultrasound gel will be applied to the scalp, gel pad, and transducer, with all visible air bubbles carefully removed. The transducer will then be affixed to the scalp via a gel pad to ensure complete contact. To maintain blinding, participants will not be shown the TUS device interface, and white noise will be delivered through earphones during stimulation to mask any device sounds. All interventions will be performed under the supervision of investigators who are also neurosurgeons specialized in neuromodulation. In the sham stimulation group, the transducer will be placed over M1, but no ultrasound will be emitted (0 W output), with the same device setup and procedures as in the active stimulation groups. Because TUS is not typically associated with distinct sensory perceptions during stimulation, participants are not expected to distinguish active from sham stimulation based on treatment sensation alone. A single sham condition will be used as a common control group for both active stimulation targets. Because participants will be assigned to only 1 treatment arm throughout the study and will not be exposed to multiple stimulation targets, differences in transducer location will not be expected to substantially affect participant blinding.

To minimize confounding effects, the initiation of new treatments for NP and alterations to existing regimens will, in principle, be prohibited from the time of enrollment until week 8. The use of rescue analgesics will be permitted during the study provided that it does not substantially deviate from the participant’s preintervention medication regimen. Participants will be instructed to maintain their existing analgesic treatment whenever possible throughout the study period. Exceptions may be permitted when required to ensure participant safety.

### Outcomes

#### Overview

The primary outcome is the change in weekly average pain intensity scores recorded in a pain diary using an 11-point NRS ranging from 0 (no pain) to 10 (worst imaginable pain). Participants will evaluate their average pain over the previous 24 hours daily at home. Weekly averages will be calculated, and changes from the baseline week to each postintervention week up to week 8 will be assessed. The primary end point is the change in weekly average pain scores from baseline to week 8. To assess clinically meaningful improvements, responder analyses will identify the proportion of participants achieving reductions of 2 points or more and 4 points or more [35] in weekly average pain scores at week 8 compared with baseline.

Secondary outcomes comprise patient-reported and physiological measures, enabling a multidimensional evaluation of pain, functional impact, psychological status, neurophysiological response, and patient perception over time. These include both longitudinal changes from baseline and postintervention assessments across the following domains.

#### Pain NRS

This will be assessed separately from the diary, with participants reporting their current pain on the same 11-point scale.

#### Short-Form McGill Pain Questionnaire Version 2

This questionnaire will evaluate the qualitative aspects of pain, with participants rating 22 items based on their current pain experience [21].

#### Brief Pain Inventory

This measure assesses pain presence, location, and intensity; analgesic use; and interference with daily life across 16 self-report items [22].

#### EQ-5D-5L

This instrument measures health-related quality of life across 5 domains [23].

#### Hospital Anxiety and Depression Scale

This scale screens for anxiety and depression using 14 items [24].

#### Pain Catastrophizing Scale

This scale assesses maladaptive cognitive responses to pain [25,26].

#### Pain Self-Efficacy Questionnaire

This questionnaire measures confidence in maintaining function despite pain [27].

#### Mini-Mental State Examination

This measure is administered by assessors to screen for cognitive impairment.

#### Quantitative Sensory Testing

This test is conducted using thermal and vibration stimulators (TSA-II and VSA-3000; Medoc) based on published methods [36]. Warm, cold, heat pain, cold pain, and vibration detection thresholds will be assessed on the volar forearm or calf of the painful side. Each session includes 2 practice and 4 formal measurements. These assessments will be performed only when the stimulation target is the upper or lower limb.

#### Motor Cortical Excitability

Evaluated using single- and paired-pulse TMS with a figure-8 coil of 70 mm, 2 Magstim 200^2^ stimulators, and a Magstim BiStim^2^ module. MEPs will be recorded from the first dorsal interosseous muscle on the painful side (Brainsight MEP module; Rogue Research Inc) elicited via contralateral M1 stimulation. Measures include resting motor threshold (RMT), short-interval intracortical inhibition, intracortical facilitation, and cortical silent period [37]. The motor hot spot is defined as the site eliciting the largest MEP and RMT as the lowest stimulation intensity evoking MEPs of 50 μV or more in at least 5 of 10 trials. Paired-pulse TMS will use a conditioning stimulus at 80% RMT and a test stimulus at 120% RMT, with interstimulus intervals of 2 ms (short-interval intracortical inhibition) and 15 ms (intracortical facilitation) plus control stimuli alone. Each stimulus will be delivered 10 times in a randomized order. The cortical silent period will be measured 10 times under 10% to 20% maximum voluntary contraction at 130% RMT, with an intertrial interval of at least 5 seconds.

#### Paresthesia (*Shibire*) NRS

Participants will rate intensity on a scale from 0 to 10. “*Shibire*” is a common Japanese term referring to abnormal sensations, such as paresthesia, dysesthesia, or numbness, and may also indicate motor difficulty, although it most often describes positive sensory symptoms such as paresthesia [28].

#### *Shibire* Questionnaire

This measure [28] evaluates the presence, quality, location, duration, intensity, and daily life impact of *shibire*.

#### Patient Global Impression of Change

This measure is administered at week 8, with participants rating overall perception of change on a 7-point Likert scale (“very much improved” to “very much worse”).

#### Adverse Events

These are defined as any unfavorable or unintended sign, symptom, or illness occurring in a participant regardless of causal relationship to the study. Worsening of preexisting conditions will also be considered adverse events.

#### Blinding Assessment

After the intervention, participants will be asked whether they believe they received real stimulation or sham stimulation or are unsure. Responses will be compared with actual treatment allocation using the Bang blinding index to assess the success of participant blinding [38].

### Statistical Analysis

Efficacy analyses will be performed on the full analysis set, defined as all randomized participants who received at least one stimulation session and had at least one postintervention outcome assessment (intention-to-treat analysis). A per-protocol set excluding participants with major protocol deviations will also be analyzed for sensitivity. Major protocol deviations will include violations of eligibility criteria identified after enrollment, withdrawal of consent, substantial nonadherence to the intervention protocol, and other deviations judged to have a significant impact on efficacy evaluation. The consistency of results between the full analysis set and the per-protocol set will be examined to evaluate the robustness of the primary findings. Any modifications or additions to the analyses after study initiation will follow an evaluation of their validity and potential impact, with corresponding amendments to the statistical analysis plan. Handling of outliers will be prespecified, and depending on the variable, either data transformation or statistical approaches robust to outliers will be applied.

Demographic characteristics and outcomes will be summarized descriptively, with longitudinal outcomes presented as line graphs over time. The primary analysis will use a linear mixed-effects model for repeated measures (MMRM) to evaluate changes in weekly average pain scores from the pain diary. The model will include change from baseline in weekly average pain scores as the response variable, with treatment group, time point, and their interaction as fixed effects and individual participants as a random effect. Baseline pain scores will be included as covariates. The primary treatment effects will be estimated using model-based contrasts comparing M1 stimulation with sham stimulation and PSI stimulation with sham stimulation at week 8. Multiplicity arising from these 2 primary comparisons will be controlled using the Dunnett adjustment. To identify time points showing significant changes from baseline, the Dunnett multiple comparison procedure will be used, with the baseline week serving as the control. The number and proportion of responders will be summarized by treatment group, and between-group comparisons will be performed using logistic regression models adjusted for baseline pain scores. Missing week 8 pain diary data will be imputed using the last observation carried forward method for responder analyses only. Secondary outcomes measured repeatedly, such as pain NRS and SF-MPQ-2, will also be analyzed using MMRM in the same way as the primary outcomes. Outcomes assessed only at baseline and week 8—including BPI, EQ-5D-5L, HADS, PCS, PSEQ, MMSE, QST, and MEP—will be evaluated using analysis of covariance, with change from baseline as the response variable, treatment group as a fixed effect, and baseline value as a covariate. Paresthesia-related outcomes will be analyzed using MMRM, analysis of covariance, or logistic regression depending on data type and timing. PGIC responses at week 8 will be summarized by treatment group and compared using the Fisher exact test. All analyses will be 2 sided, with *P* values below .05 considered statistically significant.

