### Randomization and Blinding

Participants will be randomly allocated in a 1:1:1 ratio to one of three groups: (1) active stimulation targeting M1, (2) active stimulation targeting PSI, or (3) sham stimulation. Because the primary outcomes rely on participant-reported subjective assessments, this study will adopt a single-blind design in which participants remain blinded to group allocation throughout the trial. Blinding of the investigators delivering the intervention is not feasible with the current device. As this is a preliminary study in which most outcomes are patient-reported, investigators are not blinded. To minimize expectation effects, all groups will undergo identical procedures, including treatment duration, interaction with study personnel, and auditory masking using white noise. The success of participant blinding will be evaluated at the end of the intervention period using a blinding assessment questionnaire.

Randomization will be conducted using a stratified permuted block method, with the underlying cause of NP (central or peripheral origin) as the stratification factor. The allocation table and procedure will be generated by an independent technician who is not involved in patient enrollment or outcome assessment. Assignment will be managed through the REDCap randomization module, which enhances secure handling of allocation information using password protection.

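### Randomisation is stratified by central versus peripheral pain, but the factor is absent from the mixed models and ANCOVAs, which loses power if pain origin is prognostic

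*Protocol article*

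**What the plan says.** All references are to the protocol article.

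- **Allocation (Randomization and Blinding).** "Participants will be randomly allocated in a 1:1:1 ratio to one of three groups", "using a stratified permuted block method, with the underlying cause of NP (central or peripheral origin) as the stratification factor". Origin of pain is the only stratification factor.
- **Primary model (Statistical Analysis).** Change from baseline in the weekly diary average is modelled "with treatment group, time point, and their interaction as fixed effects and individual participants as a random effect". The covariate sentence reads: "Baseline pain scores will be included as covariates".
- **Repeated secondary outcomes (same section).** Pain NRS and SF-MPQ-2 "will also be analyzed using MMRM in the same way as the primary outcomes".
- **Outcomes at baseline and week 8 only.** The ANCOVA has "change from baseline as the response variable, treatment group as a fixed effect, and baseline value as a covariate".
- **Responder analyses.** The logistic models are adjusted for baseline pain.

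Central or peripheral origin appears in none of these descriptions. The article gives no reason for leaving it out and plans no stratum-adjusted sensitivity analysis.

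**The concern.** Stratified blocks keep the arms nearly balanced on pain origin. Whatever difference in outcome exists between central and peripheral pain is therefore largely removed from the true sampling error of each active-versus-sham contrast. A linear model without origin does not know this and leaves the between-stratum variation in its residual. If that variation is real, the reported standard error is larger than the actual one, confidence intervals are too wide, and a nominal 5% test rejects less than 5% of the time under the null.

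What is at stake is efficiency. The trial plans 13 participants per arm, and its Discussion concedes that it may be underpowered. The sample size section plans 80% power for an overall one-way ANOVA, while the primary tests are two Dunnett-adjusted contrasts, which have less power under the same assumptions. Precision that the design has already secured should not be discarded in the analysis.

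**Working it through.** **1. Inputs from the Sample Size Estimation section.** Mean reduction 34.8 in each active arm and 17.4 under sham, SD 15.2, α 0.05, 80% power, 37 participants before dropout, 39 after (13 per arm).

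**2. The plan's own figure.** Grand mean = (34.8 + 34.8 + 17.4)/3 = 29.0. The mean squared deviation is (5.8² + 5.8² + 11.6²)/3 = 67.28, so Cohen's f = √67.28/15.2 = 0.540. The noncentral F distribution gives 79.7% power at N = 36 and 80.9% at N = 37. Then 37/0.95 = 38.9, rounded up to 39. The stated sample size reproduces.

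**3. Power of one primary contrast.** With 13 per arm the noncentrality is (17.4/15.2) × √(13/2) = 2.92. The two-sided Dunnett critical value for two contrasts on 36 degrees of freedom is about 2.30. Power is 72.9%.

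**4. What omission does.** Let R² be the share of the variance left after baseline adjustment that origin explains. With balanced strata:

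- the model without origin reports SE ≈ SD × √(2/n);
- the true SE is ≈ SD × √(1 − R²) × √(2/n);
- the ratio is 1/√(1 − R²), which is 1.054 at R² = 0.10 and 1.118 at R² = 0.20.

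**5. Assumptions the article does not supply.** R² from 0 to 0.20, half of participants with central pain, block size 3.

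**6. Simulation.** 6,000 trials per setting, N = 39, stratified permuted blocks, and a linear model at week 8 with and without origin. Power is for one contrast of 17.4 at the Dunnett critical value. Type I error is for one contrast at an unadjusted nominal 5%. The central–peripheral gap implied by each R², with equal strata, is 2 × √R² × 15.2.

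| R² | Implied gap | Reported SE, without / with origin | Actual SD of estimate, without origin | Power, without / with | Type I error, without |
|---|---|---|---|---|---|
| 0 | 0 | 5.93 / 5.93 | 6.03 | 72.5% / 72.3% | 4.8% |
| 0.05 | 6.8 | 5.93 / 5.78 | 5.82 | 73.4% / 74.9% | 4.4% |
| 0.10 | 9.6 | 5.93 / 5.61 | 5.61 | 73.4% / 77.3% | 3.7% |
| 0.20 | 13.6 | 5.97 / 5.31 | 5.37 | 74.0% / 82.0% | 3.0% |

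Without origin, the reported SE is too large by 5.93/5.61 = 1.06 at R² = 0.10 and 5.97/5.37 = 1.11 at R² = 0.20, in line with step 4. With origin included, type I error is about 5% throughout. The simulation error of each power figure is about √(0.73 × 0.27/6,000) = 0.6 percentage points.

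**7. Sensitivity.** Repeating the exercise with blocks of 6, with 20% or 30% central pain, and with an explicit baseline covariate left the pattern unchanged: no material change at R² = 0, a gain of about 2 points at 0.05, about 4 at 0.10 and about 8 at 0.20.

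Gaps and SEs are in the units of the sample size section, not the 0 to 10 diary scale. R² and the power figures do not depend on the unit.

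**The case against.** **The loss is conditional.** A reader might infer that the standard errors are too large and power is lost as a matter of fact. The article does not support that. It says nothing on how strongly origin predicts change in pain. Choosing a factor for stratification suggests that it may be prognostic, not that it explains 10% or 20% of the residual variance. The larger scenarios need sizeable gaps: 9.6/17.4 = 55% and 13.6/17.4 = 78% of the whole assumed treatment effect. At 5% or below the gain is 2 points or less. This stands.

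**The error is on the safe side.** A reader might also infer that the treatment comparison is biased or the test invalid. Neither follows: the estimate stays unbiased and type I error falls rather than rises. The trial is described as exploratory and not fully powered. This stands, and it makes the point one of efficiency.

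**The argument does not carry over to the logistic models.** There, omitting a prognostic factor pulls the odds ratio toward 1 and costs power. It does not enlarge the standard error. With 13 per arm and a threshold as demanding as 4 points, extra terms also risk sparse data or separation. This stands. No binary outcome was simulated.

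**The simulation is not the planned analysis.** It uses one time point, not the full mixed model, and its type I error figures are for an unadjusted test. This limits the precision of the figures, not the mechanism.

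**A separate analysis plan may include the factor.** The article refers to one that is not shown and never says that its list of terms is exhaustive. This has limited force, because the article names fixed effects and covariates model by model. Its Protocol Amendments section also records that this part of the text was revised in peer review.

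**Conclusion.** The mismatch between the stratified randomisation and the terms named for the mixed models and ANCOVAs is real. Its consequence depends on how prognostic pain origin is after baseline adjustment, which the article does not state. Over the assumed range, Dunnett power for one contrast rises with the factor by nothing at a 0% share, about 1.5 points at 5%, about 4 at 10% and about 8 at 20%. These figures rest on 39 analysed participants, the SD and effect in the sample size section, near-balanced strata and a single-time-point linear model. Validity is not threatened. Because including the factor costs no measurable power even when origin is irrelevant (72.5% against 72.3%, within simulation error), this is a free improvement rather than the correction of an invalid analysis.

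**What to change.** Add pain origin (central or peripheral, as recorded at randomisation) as a fixed effect in the MMRM for the diary, pain NRS and SF-MPQ-2, and in the ANCOVA models. In the responder logistic models, add it only where responder numbers allow, and state the rule for deciding that in advance.

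The cost is one degree of freedom per model and a short amendment to the analysis plan. The factor is already needed for allocation, so no new data are required. QST is measured only in participants with limb pain, so there the degree of freedom comes out of a smaller sample. Enrolment was ongoing at 20 of 39 on February 28, 2026, and the Statistical Analysis section provides for amendments to the analysis plan. As investigators are not blinded, the amendment should be dated and made before any comparison of outcomes by arm. If the analysis plan already contains the factor, the article's description should be brought into line with it.

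### The primary MMRM states only a participant random effect; read literally, the week-8 standard error is pooled over weeks 1–8 and is too small if the variance of change grows

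*Protocol article*

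**What the plan says.** The Statistical Analysis section of the protocol article names a mixed-effects model for repeated measures as the primary analysis. The response is "change from baseline in weekly average pain scores as the response variable". The model terms are "treatment group, time point, and their interaction as fixed effects and individual participants as a random effect", and "Baseline pain scores will be included as covariates". The primary effects are "model-based contrasts comparing M1 stimulation with sham stimulation and PSI stimulation with sham stimulation at week 8". On multiplicity and significance it states: "Multiplicity arising from these 2 primary comparisons will be controlled using the Dunnett adjustment" and "All analyses will be 2 sided, with *P* values below .05 considered statistically significant".

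No residual covariance structure, week-specific variance, random slope or degrees-of-freedom method is given. The section refers to a statistical analysis plan, which is not shown. Pain NRS and SF-MPQ-2 are to be analysed in the same manner as the primary outcome.

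**The concern.** A participant random effect with independent, equal-variance residuals implies the same variance of change at every week and the same correlation between any two weeks. Change from a baseline week often does not behave like that. A week next to baseline tends to track it more closely than a week two months later. If participants respond to repeated sessions at different rates, the spread of change widens as sessions accumulate.

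The primary question concerns week 8 alone. Under the literal model, its standard error is taken from all eight weeks. If the early weeks are less variable than week 8, the confidence intervals for the two primary contrasts are too narrow and the Dunnett-adjusted P values too small. A multiplicity adjustment cannot correct a miscalibrated standard error.

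**Working it through.** **The plan's own figure.** The article gives no error rate or weekly covariance, so its only figure to reproduce is the sample size, which sets the 13 per arm used below. The means are 34.8, 34.8 and 17.4 with SD 15.2 (Sample Size Estimation). The grand mean is 29.0 and the squared deviations are 33.64, 33.64 and 134.56, with mean 67.28. So f² = 67.28/15.2² = 67.28/231.04 = 0.291. Noncentral-F power at α = .05 is 0.797 for N = 36 and 0.809 for N = 37. Then 37/0.95 = 38.9, giving 39, or 13 per group. The figure reproduces.

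**What the literal model estimates.** With a random intercept and independent residuals, the variance of a week-8 contrast is about (2/13) × (σ_b² + σ_e²). With complete data, the estimated sum σ_b² + σ_e² is, apart from small degrees-of-freedom differences, the average of the eight weekly residual variances v₁ to v₈. Hence

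model SE / true SE ≈ √(mean of v₁…v₈ / v₈).

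The ratio is 1 if the variance is flat, below 1 if it grows and above 1 if it shrinks.

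**One case by hand (assumed values).** Let slopes vary between participants with SD 0.2 NRS points per week and let weekly noise have SD 0.8. Ignoring the baseline adjustment, v_t = 0.2²t² + 2 × 0.8² = 0.04t² + 1.28.

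- Week 1: 1.32. Week 8: 0.04 × 64 + 1.28 = 3.84.
- Mean of t² over weeks 1–8: 204/8 = 25.5, so mean v = 1.02 + 1.28 = 2.30.
- Ratio: √(2.30/3.84) = 0.77. The simulation gave 0.78.
- A Dunnett critical value of 2.227 (280 df) then acts like 2.227 × 0.774 = 1.72, which is a two-sided error of about 8.5% per contrast. Two contrasts can reach at most 17%. The simulation gave 14.9%.

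**Simulation.** There were 6000 null trials per scenario, with 13 per arm, 8 weeks and complete normal data. The random-intercept model was fitted by REML with group by week and baseline, Satterthwaite df and Dunnett critical values. The comparator is an ANCOVA at week 8 only, which uses the week-8 variance.

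| Assumed covariance | Familywise error, random intercept | Model SE / true SE | Week-8 ANCOVA |
|---|---|---|---|
| Exchangeable, ρ 0.5 / 0.8 | 4.9% / 5.2% | 0.99 / 1.00 | 4.8% / 5.4% |
| Constant response spread from week 1 | 5.1% | 1.00 | 5.0% |
| Spread shrinking after week 1 | 2.5% | 1.12 | 4.9% |
| AR(1) 0.5 | 4.8% | 0.99 | 4.6% |
| AR(1) 0.7 | 6.4% | 0.96 | 4.5% |
| AR(1) 0.8 | 8.7% | 0.90 | 4.8% |
| Spread levelling off at week 4 (SD 1.5 / 2) | 8.1% / 8.6% | 0.91 / 0.89 | 4.8% / 5.0% |
| AR(1) 0.9 | 12.6% | 0.81 | 5.5% |
| AR(1) 0.95 | 14.2% | 0.79 | 4.7% |
| AR(1) 0.98 | 15.7% | 0.77 | 5.0% |
| Slope SD 0.1 per week | 8.3% | 0.90 | 4.3% |
| Slope SD 0.2 per week | 14.9% | 0.78 | 4.7% |
| Slope SD 0.3 per week, noise SD 0.6 | 23.2% | 0.66 | 5.4% |

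Using 280 residual df instead of Satterthwaite adds up to about one point. Repeat simulations gave the same pattern, with figures differing by about a point or two: 5.5–7.4% for AR(1) 0.5 to 0.7, 12.0% at 0.90 and 13.9% at 0.95. The figures should not be read more finely than that.

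**Limits.** The covariances are assumptions. There is no dropout or stratification factor. The week-8 ANCOVA stands in for the recommended model; the unstructured REML fit with missing data and the fallback structures were not simulated.

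**The case against.** Compound symmetry is an inference. The article does not say that residuals are independent or that variances are equal, and the MMRM label usually points to a modelled residual covariance. Covariance structure, df method and convergence rules are commonly left to an analysis plan, and that plan is not shown. This stands as far as it goes: the silence on those details is no defect. What remains is that the article does state one dependence term. With an unstructured residual matrix that term would be redundant, so the label and the stated terms do not agree. An analyst following the text would fit the random-intercept model.

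A reader might infer that the two primary tests will be anticonservative, at some definite rate such as 8–14%. The document does not support this, because it gives no weekly variances or correlations. Nor is exchangeability the only safe case: error is also near 5% with AR(1) 0.5 or with constant response spread from week 1, and it falls to 2.5% if spread shrinks. Trial Schedule cites rTMS experience of relief over 4 to 8 weeks or sessions followed by a plateau. If spread levels off by week 4, the error is about 8%, well short of the highest figures; a plateau reached only near week 8 would leave spread growing through most of the window.

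The trial is also described as exploratory proof of concept and not fully powered. That lowers the consequence of a miscalibrated test. It does not remove it, since the plan declares a .05 significance threshold and adjusts the two primary comparisons for multiplicity.

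**Conclusion.** The point holds in conditional form. As written, the primary model is most naturally a random-intercept model whose week-8 standard error is pooled over weeks 1–8. Its calibration then rests on the variance of change being flat, which nothing in the article supports or excludes. Across the assumed covariances, familywise error runs from 2.5% to about 16%, and to 23% in the most extreme slope case, against 4.3–5.5% when the week-8 variance is used.

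This rests on three things: the literal reading of the random-effect wording, complete normal data with 13 per arm, and assumed covariances. It does not show that the primary results will be wrong, and it lapses if the analysis plan already sets a week-specific covariance. Should-fix.

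**What to change.** In the primary model, replace the participant random effect with an unstructured within-participant covariance across weeks 1–8, fitted by REML with Kenward-Roger df. An 8 × 8 matrix has 8 × 9/2 = 36 parameters with about 39 participants, so prespecify a fallback order that keeps week-specific variances, for example heterogeneous Toeplitz, then heterogeneous AR(1). Do not fall back to a random intercept alone for the primary contrasts. If the analysis plan already specifies this, align the article with it.

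Apply the same rule to pain NRS and SF-MPQ-2. Their visits also include weeks 12 and 16, which makes equal correlation between visits harder to defend and gives the fallback rule more to do. A baseline-by-week term is an optional refinement; its separate effect was not quantified.

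The cost is wording, possibly wider week-8 intervals, and a convergence rule. Enrollment is ongoing and the final analysis lies ahead, so the change can be made through the amendment route that the Statistical Analysis section already provides.
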